### 2.5 Questionnaires

Health behaviors and disease prevention interventions in obesity pregnant women will be assessed using a general information questionnaire and specific scales, and mental health status will be measured by 7-item generalized anxiety disorder (GAD-7) (27), and the Self-Efficacy Scale, which reflect participants' anxiety, self-rated status, and stress levels over the past 2 weeks. Sleep quality will be assessed using the Pittsburgh sleep quality index (PSQI), including sleep quality, time to fall asleep, sleep duration, sleep efficiency, sleep disorders, hypnotic drugs, and daytime dysfunction. The level of physical activity will be assessed using the Physical Activity Rating Scale-3 (PARS-3). This scale evaluates the intensity, duration, and frequency of physical activity over the past month. The Family Health Scale short-form (FHS-SF) will be used to measure the social and family support component, which has high reliability and validity (28). The physical and mental health status of the obese comorbidity population will be based on the five-level five-dimensional health scale, and the World Health Organization's five physical and mental health indicators (WHO-5). The health status is judged by five dimensions: mobility, self-care, daily activities (such as work, study, housework, family or leisure activities), pain or discomfort, anxiety or depression, so as to propose targeted solutions to obesity-related factors. Health literacy will be assessed using Healthy Lifestyle Scale-Short Form 4 (HLS-SF4) that evaluates the ability to access, understand, and apply health-related information. Perceived stress will be measured using the Perceived Stress Scale (PSS), which assesses the frequency of feelings and thoughts related to stress over the past month. Social support will be evaluated using Perceived Social Support Scale that measures the perceived availability of emotional and practical support from family, friends, and significant others. The scale assesses the extent to which individuals feel cared for and supported in their personal and social lives (Table 1).

**Table 1 T1:** Variables and measures collected at evaluation time points.

**Variables**		**Data source**	**Measures**	**Follow-up time point**					
				**T-0**	**T-1**	**T-2**	**T-3**	**T-4**	**T-5**
Covariates	Individual	Survey	Age, marital status, education level, occupation, annual income, ethnicity	√					
Social and demographic factors	Family related factors	Survey	Parents' medical history of hypertension, diabetes, and cardiovascular disease, annual family income	√					
Health status		Survey and Medical record	Height, weight, BMI, blood pressure and blood sugar, smoking and drinking status, WHO−5	√	√	√	√	√	√
Activity	Physical activities	Survey	Physical Activity Rating Scale-3, PARS-3	√	√	√	√	√	√
Psychosocial status	Quality of life	Survey	EQ-5D version, EQ-5D-5L	√	√	√	√	√	√
	Sleep	Survey	Pittsburgh sleep quality index, PSQI	√	√	√	√	√	√
	Social support	Survey	Social support rate scale, PSSS-SF	√	√	√	√	√	√
Psychology status	Anxiety	Survey	General Anxiety Disorder-7, GAD-7	√	√	√	√	√	√
	Stress	Survey	Perceived Stress Scale, PSS-4	√	√	√	√	√	√
	Self-efficacy	Survey	General Self-Efficacy Scale	√	√	√	√	√	√
	Family health	Survey	The Family Health Scale short-form, FHS-SF	√	√	√	√	√	√
Cost-effectiveness	Tracking cost	Survey and medical record		√	√	√	√	√	√
Qualitative results			Effect of trial	√	√	√	√	√	√

### 2.6 Statistical analysis

Participants' socio-demographics are presented as count and proportion, and the χ^2^ test was used to assess categorical variables. The continuous variables normally distributed were assessed by the student's *t*-test. The Fisher's exact or the chi-square test was adopted for categorical data, and statistical significance was set at *p* < 0.05. The main analysis was performed using generalized estimating equations (GEE) model. The GEE solved the problem of correlation of longitudinal data, utilizing the results of each measurement in the longitudinal data, which greatly reduces the loss of information (20). To clarify whether socioeconomic status affects the effectiveness of ILSM, we conducted several subgroup analyses for physiological health outcomes and health behaviors, and added the interaction terms to generalized estimating equations model to assess the interactions between time (at baseline, 3-month, 6-month, and 18-month) and group (intervention and control). We also used GEE to analyze the health benefits of intervention and control groups among participants with different socioeconomic status. Significance level of the associations in the final model was set at *P*-value 0.05. The data were analyzed using SPSS 20.0 (IBM Corporation, Armonk, NY, USA).

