#### 2.1.1 Sample size

As this study is a randomized controlled trial, the respondents will be divided into manual intervention group, artificial intelligence (AI) intervention group, artificial intelligence and manual combined intervention group, and observe the BMI of pregnant women, maternal weight and maternal adverse pregnancy outcomes as the main outcome indicators. The sample size was calculated based on an expected effect size of 0.5, which corresponds to the minimal clinically important difference (MCID) of the primary outcome. This MCID was determined based on previous literature and clinical judgment. Setting bilateral α = 0.05, the degree of certainty was 90%. Using the PASS15 software, we obtained a sample size of N1 = 40 cases for the group and N2 = 40 cases for the group and N3 = 40 cases for the group. For a total of at least 120 subjects to be included in the study.

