### 2.4 Outcomes

#### 2.4.1 Primary outcomes

The primary outcomes of the study include maternal body mass index (BMI), maternal weight, and adverse pregnancy outcomes. The primary outcome measures (such as BMI, maternal weight, and adverse pregnancy outcomes) will be assessed using Repeated Measures ANOVA or Mixed Effects Models to evaluate the intervention effects. For long-term effect analysis, Generalized Estimating Equations (GEE) or Cox Proportional Hazards Models will be employed to assess the short-term, medium-term, and long-term impacts of the interventions. Cost-effectiveness analysis will be conducted using Quality-Adjusted Life Years (QALY) and Incremental Cost-Effectiveness Ratios (ICER) to evaluate the economic efficiency of different intervention measures, with sensitivity analysis performed to verify the robustness of the results.

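### GEE is named as the main analysis with 40 women per arm, against the mixed model named for BMI and weight; an uncorrected robust joint group-by-time test would run at about 7-11%, not 5%

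*Protocol article*

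**What the plan says.** Section 2.6 names the method: "The main analysis was performed using generalized estimating equations (GEE) model". It says the authors "added the interaction terms to generalized estimating equations model to assess the interactions between time" and group, listing four times (baseline, 3, 6 and 18 months) and two groups (intervention and control). On the threshold it says "Significance level of the associations in the final model was set at" a P-value of 0.05. It names no working correlation, variance estimator, test statistic or small-sample method.

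Section 2.4.1 says that BMI, maternal weight and adverse pregnancy outcomes "will be assessed using Repeated Measures ANOVA or Mixed Effects Models to evaluate the intervention effects". It reserves GEE, or a Cox model, for long-term effects.

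Section 2.1.1 fixes the numbers: "we obtained a sample size of N1 = 40 cases for the group and N2 = 40 cases for the group and N3 = 40 cases" for the third group, and "For a total of at least 120 subjects to be included in the study".

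The article gives three versions of the time factor: four times in section 2.6, five in section 2.1 (baseline, 20, 28 and 36 weeks, and postpartum), and six in Table 1 (T-0 to T-5). The design has three arms; section 2.6 speaks of two groups.

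**The concern.** There are two linked problems. First, the article gives two different answers to the question of which model is the main one for BMI and weight.

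Second, one of those answers suits this sample size less well. Inference from GEE with the sandwich variance is a large-sample method. With few women per arm the sandwich variance is too small on average, and a chi-square reference ignores the fact that the variance was estimated. Both errors push towards rejection, and they grow with the degrees of freedom of the test. A joint test of group by categorical time has (groups - 1) x (times - 1) degrees of freedom: 3 on section 2.6's own wording, and 8 or 10 with three arms at five or six visits. Each arm's covariance matrix comes from only 40 women.

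At stake is whether a joint test reported at 0.05 has that error rate, before any allowance for multiplicity.

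**Working it through.** **Inputs from the article.** 40 women per arm (2.1.1); three arms (2.1.1, 2.2) or two groups (2.6); four times (2.6), five (2.1) or six (Table 1); threshold 0.05 (2.6).

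**Assumptions, not in the article.** Uncorrected robust covariance, Wald chi-square test, categorical time, complete normal data, within-woman correlation 0.7 (exchangeable) or 0.8 (AR(1)).

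**The plan's own figure.** Section 2.1.1 says "The sample size was calculated based on an expected effect size of 0.5" and "Setting bilateral α = 0.05, the degree of certainty was 90" per cent. Read as a standardised difference between two arms, n = 2(1.960 + 1.282)²/0.5² = 84.06, so 85 per arm. At 40 per arm, power = Φ(0.5 × √20 - 1.960) = Φ(0.276) = 61%. The 40 is therefore not reproduced on this reading. That is a separate matter; 40 is used here only because it is the number of women per arm that the plan fixes.

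**Test statistic.** With saturated arm-by-visit means and complete data, the GEE estimates are the cell means. The robust covariance in arm g is V_g = Σ(residual cross-products)/n². With C picking out the interaction, W = (Cb)′(CVC′)⁻¹(Cb), compared with chi-square on (G - 1)(T - 1) degrees of freedom.

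**Exact check for two groups.** With equal covariances, W = T² × n/(n - 1), where T² is Hotelling's statistic. With p = T - 1 and ν = 2n - 2 = 78, T²(ν - p + 1)/(pν) follows F(p, ν - p + 1).
- Four times, p = 3: the chi-square limit 7.815 becomes T² = 7.815 × 39/40 = 7.619. Then F = 7.619 × 76/(3 × 78) = 2.475, and P(F(3,76) > 2.475) = 6.8%.
- Five times, p = 4: limit 9.488, F = 2.224 on (4,75), 7.4%.
- Six times, p = 5: limit 11.070, F = 2.048 on (5,74), 8.2%.
- One contrast, p = 1: limit 3.841, F = 3.745 on (1,78), 5.7%.

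**Simulation under the null, 40 per arm, nominal 5%** (20,000 trials per cell, Monte Carlo standard error about 0.2 points; fitted GEE 5,000 trials).

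| Robust Wald joint test | 4 times | 5 times | 6 times |
|---|---|---|---|
| Two groups (3, 4, 5 df) | 7.0% | 7.2% | 8.4% |
| Three arms (6, 8, 10 df) | 8.0% | 9.6% | 10.8% |
| Three arms, fitted GEE, exchangeable working correlation | 7.9% | 9.1% | 10.9% |
| Three arms, AR(1) data | 8.3% | 9.4% | 10.7% |
| Three arms, t5 errors | 7.9% | 8.6% | 10.2% |

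**Other choices that section 2.6 also permits, three arms.**
- Single interaction coefficient or single-visit contrast: 5.2-6.1%.
- Linear time (2 df): 5.4-6.2%.
- Model-based standard errors with the right working correlation: about 4%. With a wrong one (AR(1) data, exchangeable working, five times): 7.1%.

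**Remedies for the three-arm joint test, at 4, 5 and 6 times.**
- GEE with Kauermann-Carroll-type scaling and an F reference: 6.2%, 7.4%, 7.9%.
- GEE with Mancl-DeRouen-type scaling and chi-square: 6.5%, 7.8%, 8.6%.
- REML mixed model, unstructured covariance, Satterthwaite degrees of freedom: 5.4-5.9%.
- Multivariate F test on the same data: 4.8-5.2%.

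**The case against.** The strongest reply is that the article never commits to the test simulated here. It says only GEE. The covariance estimator, the reference distribution and any small-sample correction are details that an article normally leaves to the analysis plan, so their absence is not an error. Some choices compatible with the text run near 4-6%. This stands, and the inflation has to be stated as conditional.

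A second reply is that the interaction terms appear in a sentence about socioeconomic status, beside subgroup analyses, so the joint test is not shown to be the one that decides the trial. This also stands.

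A reader might go further and infer that the stated 5% level fails outright, or that false positives run at twice the nominal rate. The article does not support that. About twice is the upper end, reached with three arms at five or six visits and an uncorrected robust joint test. Section 2.6's own four times and two groups give about 7%.

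A reader might also argue against GEE because of informative dropout. The article gives no dropout rate, mechanism or working correlation from which to size such a bias, and its remark about loss of information concerns using every repeated measurement. That argument is not made here.

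None of these replies removes the conflict between sections 2.4.1 and 2.6, which lies in the text itself and is not a detail left for later.

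**Conclusion.** The point holds in conditional form. The article names two different main analyses for BMI and weight. The one named in section 2.6 is the more fragile at 40 women per arm: the uncorrected robust joint group-by-time test runs at about 7-8% with two groups, about 8% with three arms at four times, and about 9-11% with three arms at five or six visits. The direction is stable across the correlation structures and error distributions tried. The size rests on the robust Wald chi-square test being used uncorrected and on time being categorical. Single-visit contrasts, at about 5-6%, are little affected, so if the primary comparison were one visit the practical effect would be small.

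**What to change.** Reconcile sections 2.4.1 and 2.6 by stating one main analysis for weight and BMI: the mixed model already named in 2.4.1, with visit as a category, arm by visit, unstructured within-woman covariance, REML, and Satterthwaite or Kenward-Roger degrees of freedom. State the arms and visits that enter the model, since the test's degrees of freedom depend on them.

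Keep GEE as a sensitivity analysis, with a bias-corrected sandwich variance and an F or t reference. Say plainly that this restores the 5% level only in part: the three-arm joint test still ran at about 6-8% with the F reference.

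The change concerns weight and BMI only; adverse pregnancy outcomes need their own stated method. The cost is a change of wording, a few lines of code and slightly less favourable p-values. No new data are needed. Confirm that the named software version offers the chosen degrees-of-freedom method.

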##### 2.1.2.2 Exclusion and withdrawal criteria

The following exclusion criteria were applied to the patient samples in this study: pregnancies resulting from assisted reproductive technology; individuals on bed rest; patients with a diagnosis of diabetes mellitus or gestational diabetes mellitus; those with uncontrolled hypertension; individuals with a recent diagnosis of thyroid disease within the preceding 30 days; subjects with a history of cardiovascular, oncological, pulmonary, or severe gastrointestinal diseases; participants with a history of eating disorders or bariatric surgery; individuals with serious mental illnesses; those with a recent history of mood or anxiety disorders; patients with substance abuse or alcohol use disorders; pregnancies beyond 13 weeks of gestation.

Additionally, the following samples were excluded from the study: participants who withdrew from the study; individuals experiencing severe acute diseases requiring treatment during the study period.

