#### 2.7.2 Research implementation phase

The study will rigorously enforce the inclusion criteria for survey subjects, ensuring a meticulous selection and inclusion process into the study cohort. Participants with obesity pregnant women and their families will receive brochures detailing the prevention and treatment of chronic diseases, and informed consent will be obtained to ensure the authenticity of the feedback and to maintain a high response rate. Reminders will be sent via phone calls or text messages to minimize loss to follow-up during the survey process. Surveyors are committed to upholding principles of objectivity and equality, introducing the study's purpose and significance to each participant prior to commencing the survey and obtaining their informed consent. Furthermore, to ensure data integrity, the survey questionnaires will undergo regular review by auditors, with any inconsistencies or issues being addressed through immediate verification and correction.

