Next are the differences with the existing literature. Notably, our cost-benefit analysis revealed that the AI-only intervention offered a scalable solution with moderate efficacy, whereas the combined AI+Manual group achieved the highest clinical impact. This contrasts with Perdomo et al., who emphasized surgical and pharmacological interventions as primary strategies for severe obesity (15). However, our results align with Sallam et al., where TLC combined with medication synergistically improved metabolic outcomes (20). Such parallels suggest that hybrid models (AI + human expertise) may bridge the gap between resource-intensive and purely automated interventions.

However, this study has the following limitations. First, despite the high coverage rate of smartphones in China, some patients may not be able to use them well, which may hinder the implementation and reduce the effectiveness of AI interventions. Second, for the collection of the primary and secondary outcomes, we primarily used questionnaire indicators, which may inevitably lead to recall bias. Third, due to the lack of balanced stratification, comparative analyses between subgroups may not be suitable if the sample size of each group is insufficient across groups (e.g., compare the differences and potential influencing factors of AI-TLC intervention effects in different age groups). Fourth, the short-term follow-up period (up to 3 months postpartum) precludes conclusions about long-term weight maintenance. Meta-analyses of lifestyle interventions for obese pregnant women indicate that postpartum weight retention remains a challenge beyond 12 months (35), emphasizing the need for extended follow-up in future studies. Additionally, socioeconomic disparities in AI accessibility—particularly among older or rural populations—may limit generalizability, necessitating stratified analyses in broader cohorts.

Despite these limitations, this study may provide a scientific basis for developing personalized and effective interventions to further improve the health behavior and health of obesity pregnant women. It is expected to provide a new perspective and effective approach to the management of obesity pregnant women.

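### GEE is made the main analysis because it uses every measurement, but that does not protect the weight and BMI contrast if weight-related dropout differs by arm; the mixed model already named in 2.4.1 needs less

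*Protocol article*

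**What the plan says.** Two sections of the protocol article name a method for the same primary outcomes, and they differ.

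- Section 2.6: "The main analysis was performed using generalized estimating equations (GEE) model". The reasons given are that GEE deals with the correlation of longitudinal data and has the merit of "utilizing the results of each measurement in the longitudinal data, which greatly reduces the loss of information".
- Section 2.4.1: BMI, weight and adverse pregnancy outcomes "will be assessed using Repeated Measures ANOVA or Mixed Effects Models to evaluate the intervention effects". GEE appears there in another role: "For long-term effect analysis, Generalized Estimating Equations (GEE) or Cox Proportional Hazards Models will be employed".

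Three other places bear on missing data. Section 2.7.2 foresees some loss: "Reminders will be sent via phone calls or text messages to minimize loss to follow-up during the survey process". Section 2.1.2.2 says that "the following samples were excluded from the study: participants who withdrew from the study". Section 2.1.1 sets 40 women per arm and states no allowance for dropout. No working correlation, weighting, imputation or missing-data assumption is stated anywhere.

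**The concern.** Using every row that was observed is a gain in information. It does not make the estimate valid when the unobserved rows are a selected set. A reader of 2.6 could take the stated advantage of GEE as an answer to dropout, which it is not.

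The two named methods also differ in what they need. GEE with no weighting or imputation is guaranteed consistent only if missed visits are unrelated to earlier weights, given the covariates in the model. A mixed model fitted by likelihood needs only missingness that depends on observed data, together with an adequate mean and covariance model. So the conflict between 2.4.1 and 2.6 is more than a matter of labels.

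What is at stake is the arm contrast in weight and BMI. If women who have gained more leave one arm more readily than another, the women who remain make that arm look better. A small-sample correction to the GEE standard error does not remove this.

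**Working it through.** **1. Inputs.** From the article: GEE as main analysis (2.6); mixed models as an option for the same outcomes (2.4.1); visits at about 12, 20, 28 and 36 weeks and postpartum (2.1); 40 per arm and an effect size of 0.5 (2.1.1). The article gives no dropout rate, SD or within-woman correlation, so there is no stated figure to reproduce. Everything numerical below is an assumption.

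**2. Where the bias comes from.** Take independence GEE with a separate mean for each arm and visit. The fitted mean is the mean of the women still observed. If a proportion p is lost and the lost women would have gained D kg more than those retained, that arm's mean is shifted by −p × D. The bias of the contrast is the difference between these shifts. It cancels when p × D is the same in both arms and vanishes when D = 0. Unequal dropout alone is therefore not enough. A working correlation close to the truth lets a lost woman's earlier weights inform her later mean, which removes most of the shift.

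**3. Growth-model simulation, true difference zero.** Assumed: woman-level SD 12 kg, random gain SD 4.8 kg at 36 weeks, residual SD 1 kg. Dropout depends on the last observed gain in the AI arm and is random (10%) in the Manual arm. Spurious benefit for AI at 36 weeks, in kg:

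| Setting | Independence GEE | Exchangeable GEE | Likelihood mixed model |
|---|---|---|---|
| 40 per arm, log-odds 1.0 per SD of gain, about 23% lost | 0.59 | 0.49 | 0.03 |
| 40 per arm, log-odds 1.5, about 22% lost | 0.87 | 0.64 | 0.03 |
| 40 per arm, log-odds 1.0, about 32% lost | 0.81 | 0.66 | 0.01 |
| 200,000 per arm, same model, 23-35% lost | 0.67-0.97 | 0.53-0.72 | 0.03 or less |
| 200,000 per arm, similar growth model, 19-30% lost | 0.27-0.42 | 0.22-0.30 | 0.03 or less |

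The Monte Carlo standard error in the 40-per-arm rows is 0.03-0.06 kg. In the last setting the bias was near zero once both arms had the same dependence. Unstructured GEE gave 0.28 and 0.38 kg in the first two settings and was not run in the third. A large-sample version had an estimated matrix that was not positive definite, so little weight belongs on those figures.

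As a gauge of strength, inverting step 2 for the first row gives D = 0.59 / 0.23 = 2.6 kg. The women lost would have gained at least about 2.6 kg more than those retained.

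**4. Constant-variance simulation.** Assumed: 200,000 per arm, outcome in SD units, true correlation exchangeable 0.8 or AR(1) 0.9, mostly 20-30% lost. Bias at the last visit:

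- Dropout unrelated to weight, even 10% against 29% by arm: about 0.
- Same dependence on weight in both arms: 0.00-0.02 SD with independence GEE.
- Heavier women lost in one arm only: 0.12 SD with independence GEE.
- Opposite direction by arm: 0.23-0.26 SD with independence GEE, and 0.40-0.45 SD in a strong case.
- Exchangeable or unstructured GEE: at most 0.03 SD throughout.
- AR(1) GEE: at most 0.04 SD if AR(1) is true, up to 0.15 SD if not.
- Likelihood: 0.01 SD or less.

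Steps 3 and 4 differ for exchangeable GEE because in step 3 women diverge as gain accumulates, so a constant-variance exchangeable matrix is wrong there. In step 4 it is right or close enough.

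**5. Scale.** In the step 3 model the SD of gain is √(4.8² + 1² + 1²) = 5.0 kg and the SD of weight is √(12² + 4.8² + 1²) = 13.0 kg. A bias of 0.22-0.87 kg is then 0.04-0.17 SD of gain but only 0.02-0.07 SD of weight. Section 2.1.1 does not say which scale its 0.5 refers to.

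**6. Withdrawn women.** In the step 4 model, analysing completers only gave a last-visit bias of 0.12-0.45 SD in the arm-differential cases, the same as independence GEE. The completers' change from baseline was biased by at most 0.035 SD there, because dropout was made to depend on the level of weight. The change-score result need not carry over to step 3, where dropout depends on gain.

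**The case against.** The case against is substantial.

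- **Silence on detail.** The article is condensed. Weighting, imputation and the working correlation may be set out in a document that is not shown, and their absence here is no fault. That GEE is unweighted is an inference. This stands.
- **The bias is conditional.** It needs dropout that depends on weight differently by arm, and a working correlation far enough from the truth. The article fixes neither. This stands, so the point is that GEE can bias the contrast, not that it does.
- **The mechanism is assumed.** A reader might infer that nobody follows up the AI-only arm. Section 2.3 separates the arms by who produces the plan, Section 2.1 gives one visit schedule, and the reminders in 2.7.2 are not restricted by arm. Table 1 takes weight and BMI from medical records as well as surveys, so a woman who stops self-reporting need not have missing weights.
- **The Discussion does not predict dropout.** Its remark on poor smartphone use, "which may hinder the implementation and reduce the effectiveness of AI interventions", concerns effectiveness and not missed visits.
- **Section 2.6 claims only less loss of information.** It does not say that GEE is valid under selective dropout. This is correct, although the claim is the main ground offered for the choice.

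What survives is that 2.6 positively names a main method, the reason given does not bear on selective dropout, and 2.4.1 already names a method with a weaker requirement.

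**Conclusion.** The concern holds in a conditional form. Sections 2.4.1 and 2.6 name different methods for weight and BMI, and the one called the main analysis has the stronger missing-data requirement unless it is weighted or combined with imputation. If weight-related dropout differs by arm and the working correlation is wrong, the contrast at 36 weeks could be off by about 0.2-0.9 kg under independence or exchangeable GEE with some 20-30% lost in one arm. The largest single figure was 0.97 kg, in runs with up to 35% lost. The likelihood mixed model stayed within 0.03 kg. The GEE bias is near zero when dropout is unrelated to weight or equally related in both arms.

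These sizes rest wholly on assumed dropout, SDs and growth. It would be tempting to state the bias as a share of the design effect size of 0.5, but the article does not give that figure's scale and the share changes by a factor of 13.0 / 5.0 = 2.6 between the two natural choices. Nor do the documents support saying that GEE is unbiased only under completely random missingness. The accurate statement is that its consistency is guaranteed only when missed visits do not depend on earlier weights given the covariates.

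**What to change.** - **Section 2.6.** For weight and BMI, make the mixed model of 2.4.1 the single main analysis: restricted maximum likelihood, three arms by visit, unstructured within-woman covariance, all observed visits of all randomised women. Use the visits of Section 2.1, since 2.6 now writes its interaction for two groups and a different set of times.
- **Section 2.4.1.** Drop the repeated measures ANOVA alternative for weight and BMI, so that both sections name the same model.
- **GEE.** Keep it as a sensitivity analysis, preferably weighted by the inverse probability of remaining under observation, with its working correlation stated.
- **Section 2.1.2.2.** Change the text so that data observed before withdrawal stay in the analysis. Read literally, it removes these women, and no model can recover deleted data.
- **Rationale.** Do not present the use of every measurement as protection against dropout.

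The cost is a few sentences. The same data are used and the method is already in the plan. The small downside is reliance on normal-theory modelling and on a correctly specified covariance.
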